## Sample size

The sample size of 192 infants assumes 10% lost to follow-up due to withdrawal and infant deaths, meaning there will be an estimated 86 evaluable infants per group at endline. This sample size provides 86% power at 5% significance to detect a 20% increase in the proportion of infants achieving their recommended energy intake (by 24-hour dietary recall) in the IYCF-plus arm, assuming that only 65% of infants are meeting requirements in the IYCF (standard-of-care) arm based on SHINE data. If lost to follow-up is as high as 15%, we will still have 80% power to detect a 20% increase in the proportion reaching their daily energy intake (study primary outcome).

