We recently conducted the Sanitation Hygiene Infant Nutrition Efficacy (SHINE) trial,^5^ a 2×2 factorial cluster-randomised trial of improved water, sanitation and hygiene and improved IYCF in rural Zimbabwe. A combination of IYCF messages and provision of SQ-LNS between 6 and 18 months of age improved LAZ of children at age 18 months by+ 0.16 (95% CI 0.08 to 0.23) and reduced stunting by 20%.^5^ The intervention also increased haemoglobin by 2.0 g/L (95% CI 1.3 to 2.8) and reduced anaemia by almost 25%.^5^ However, despite this intensive IYCF intervention, 32%, 73% and 23% of infants did not meet energy, folate and zinc/iron dietary intake requirements, respectively, as determined by 24-hour recall in a subgroup at 12 months and over one-quarter remained stunted. We also found evidence for barriers to infant nutrition, including caregiver capabilities,^6^ household characteristics,^5^ infant enteropathogen carriage,^7^ and systemic and intestinal inflammation,^8 9^ which were not resolved by the IYCF intervention.^10^ Thus, we believe that persistent barriers to nutrient intake, uptake and utilisation limited the impact of the IYCF intervention.

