## Randomisation

The randomisation schema was preprepared by the trial statistician using the RALLOC command in STATA V.14, using random permuted blocks of varying block sizes, with a 1:1 allocation to IYCF or IYCF-plus. Randomisation codes are securely embedded in the trial database so that the next number is accessible to the data officer, but not the entire randomisation list. Participant IDs were pregenerated and allocated to treatment arms prior to recruitment into the study. Participant IDs were assigned to a specific participant within a household after consent. Twins or eligible infants within the same household were allocated to the same trial arm. One of each twin were randomised to a specific arm. The CHW, supervised by an IN, visited the mother to tell her the trial allocation and to begin the interventions. It was not possible to blind households or fieldworkers to the interventions, but data and laboratory analysts are blinded to the allocated arm. All laboratory and data analyses will be identified by participant ID number, which does not contain details of the trial arm, and then merged by the trial statistician before reporting. Monthly reports of adverse events were reported to an independent trial safety monitor and to the Medical Research Council of Zimbabwe.

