## Statistical analysis

Analysis of trial outcomes will be by intention to treat. P values will be two sided and interpreted as significant if p<0.05. Binary outcomes will be compared between groups using the χ^2^ test and logistic regression to compute ORs and corresponding 95% CIs. Other categorical outcomes with more than two levels will be compared between groups using χ^2^ tests and multinomial regression. Continuous outcomes will be compared using simple t-tests and linear regression. Non-normal continuous outcomes will be transformed appropriately before analysis. Robust SE estimates will be used to estimate CIs.

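### The 86% and 80% powers do not match at the sample sizes stated: the test that gives 86% at 86 per arm gives about 85%, not 80%, at 15% loss

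*Protocol article*

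**What the plan says.** All of the power figures stand in the Sample size section of the protocol article.

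- Base case: "The sample size of 192 infants assumes 10% lost to follow-up due to withdrawal and infant deaths". The section puts the number left for analysis at 86 in each arm.
- Headline power: "This sample size provides 86% power at 5% significance to detect a 20% increase in the proportion of infants achieving their recommended energy intake". The control rate behind it is given as a planning assumption: "assuming that only 65% of infants are meeting requirements in the IYCF (standard-of-care) arm based on SHINE data".
- Higher loss: "If lost to follow-up is as high as 15%, we will still have 80% power to detect a 20% increase".

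The section names no test or formula, gives no target proportion for the IYCF-plus arm, and does not say whether 20% is absolute or relative. Other sections supply the remaining inputs. Under Statistical analysis, "P values will be two sided and interpreted as significant if p<0.05", and binary outcomes are compared by a chi-squared test and logistic regression. Under Randomisation, allocation is "with a 1:1 allocation to IYCF or IYCF-plus".

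**The concern.** Going from 10% to 15% loss removes only four or five infants per arm (86.4 to 81.6). A fall in power from 86% to 80% is too large for so small a change, so at least one of the two figures appears to belong to another test or another number of infants.

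These are the only power figures in the article. If the 86% is sound, the 15%-loss figure is understated and makes the design look more sensitive to dropout than it is. If the 80% is sound, the headline figure is overstated. The text gives no way to tell which. The bare phrase about a 20% increase adds to the difficulty, because a relative rise from 65% would be to 78%, a much smaller effect.

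**Working it through.** **Inputs.** Control proportion p1 = 0.65 (Sample size). Target p2 = 0.85 if the 20% is absolute. Two-sided 5%, so z = 1.96 (Statistical analysis). Allocation 1:1 (Randomisation). Per arm: 192 × 0.90 / 2 = 86.4, stated as 86; at 15% loss, 192 × 0.85 / 2 = 81.6, so 81 or 82.

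**Formula (uncorrected two-proportion test, pooled variance under the null).**

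Power = Φ{ [ (p2 − p1)√n − 1.96 √(2 p̄(1 − p̄)) ] / √( p1(1 − p1) + p2(1 − p2) ) }, with p̄ = 0.75.

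The two fixed terms are 1.96 × √(2 × 0.75 × 0.25) = 1.200 and √(0.2275 + 0.1275) = 0.596.

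**Step 1: reproduce the 86%.** At n = 86: 0.20 × √86 = 1.855; (1.855 − 1.200) / 0.596 = 1.098; Φ = 86.4%. This agrees with the stated figure.

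**Step 2: same formula at 15% loss.** At n = 81.6: 0.20 × √81.6 = 1.807; (1.807 − 1.200) / 0.596 = 1.018; Φ = 84.6%. At 81 per arm it is 84.3% and at 82 it is 84.7%. The stated figure is 80%.

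**Step 3: where this formula gives 80%.** At n = 73 power is 80.3%. That is a total loss of 1 − 73/96 = 24%. It is also what results from taking 15% off the 86 that already allow for 10% loss: 86 × 0.85 = 73.1.

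**Step 4: other methods, 65% vs 85%, two-sided 5%.** The continuity correction subtracts 1/n from the difference.

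| Method | 96 per arm (no loss) | 86 per arm | 82 per arm | 81 per arm |
|---|---|---|---|---|
| Uncorrected, pooled | 89.9% | 86.4% | 84.7% | 84.3% |
| Uncorrected, unpooled | 90.8% | 87.6% | 86.0% | 85.6% |
| Arcsine | 90.3% | 87.0% | 85.4% | 85.0% |
| Exact power of the chi-squared test | 90.4% | 87.1% | 85.3% | 84.8% |
| Continuity-corrected | 86.5% | 82.1% | 80.0% | 79.4% |
| Fisher's exact test | 87.5% | 82.6% | 80.8% | 80.2% |

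The uncorrected methods give 86% to 88% at 86 per arm and 84% to 86% at 15% loss. The corrected and Fisher methods give about 80% at 15% loss, but 82% to 83% at 86 per arm. Within each method the step from 86 to 81 or 82 per arm costs about 1.5 to 3 points, not 6.

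**Step 5: absolute or relative.** A relative rise of 20% is 0.65 × 1.2 = 0.78. The uncorrected formula then gives 47.1% at 86 per arm and 45.2% at 81.6. Only the absolute rise to 85% yields the stated 86%.

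**The case against.** The strongest defence is that the headline figure is correct. It reproduces under the kind of test that the Statistical analysis section names for binary outcomes, and the word *still* in the 15% sentence can be read as a floor: power does not fall below the conventional 80%. Under the uncorrected test that is true, since power is about 85%. This stands as far as adequacy goes, because on this reading nothing is overclaimed. It does not make the pair consistent. The sentence gives 80% as a figure beside 86%, and 80% is also almost exactly the continuity-corrected or Fisher value at 81 to 82 per arm, a reading under which the 86% would be too high.

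A reader might infer that the two powers cannot come from one formula at all. The documents do not support that. The continuity-corrected formula gives 86.5% at 96 per arm (all 192, no loss) and 80.0% at 82. The uncorrected formula gives 86.4% at 86 and 80.3% at 73. Each route, however, attaches one power to a number of infants other than the one the section gives for it.

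A reader might also infer that true power is 47%, from the relative reading. The wording does allow it, but the 86% itself settles the point: with 65% and 86 per arm, only a 20-point rise fits.

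Finally, a reader might infer an error in the 65%, because the Introduction reports of SHINE that "32%, 73% and 23% of infants did not meet energy, folate and zinc/iron dietary intake requirements", so that 68% met the energy requirement. That figure is from a subgroup at 12 months, whereas this trial's outcome is at 9 to 11 months, so the two need not agree. With the stated 20-point increase, 68% to 88% gives 89.3% at 86 per arm, so the difference does not undermine the power claim.

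**Conclusion.** The point holds in limited form: at the sample sizes the section states, the two powers do not match. If the uncorrected test was used, the 86% is right and the 15%-loss figure should be about 85%, so the 80% is about 5 points too low. If a continuity-corrected test was used, the 80% is right and the 86% should be 82%, about 4 points too high. The article does not name the method, so which figure needs changing cannot be settled from it. The chi-squared test in the analysis section and the exact match at 86 per arm favour the first.

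This rests on p1 = 65%, an absolute 20-point rise, two-sided 5%, 1:1 allocation and loss counted from 192. It concerns only the stated comparison of proportions. It does not show that the power statement as a whole is wrong or that the trial is too small: power at 15% loss is about 80% or higher under every method in the table.

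**What to change.** Restate the section with one method throughout. For the uncorrected test: 86 evaluable infants per arm give 86% power (two-sided 5%, uncorrected chi-squared test) to detect an absolute rise of 20 percentage points, from 65% to 85%; at 15% loss (81 to 82 per arm) power is about 85%. If a continuity-corrected calculation was intended, give the pair as 82% and 80% and name the correction. If the 80% was meant as a floor, or for about 73 per arm, say so and give that number.

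A short note on which SHINE data the 65% comes from would be helpful but is optional.

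The cost is a text correction to one section. Enrolment, which is already complete, and the analysis do not change.

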## Statistical analysis

Analysis of trial outcomes will be by intention to treat. P values will be two sided and interpreted as significant if p<0.05. Binary outcomes will be compared between groups using the χ^2^ test and logistic regression to compute ORs and corresponding 95% CIs. Other categorical outcomes with more than two levels will be compared between groups using χ^2^ tests and multinomial regression. Continuous outcomes will be compared using simple t-tests and linear regression. Non-normal continuous outcomes will be transformed appropriately before analysis. Robust SE estimates will be used to estimate CIs.

The primary outcome, percentage of infants meeting energy intake (kcal/day), will be calculated using measured intake data from dietary recalls from all participants. Dietary energy intake (DEI) was collected through an interactive, multiple-pass, 24-hour recall at the 9-month endpoint among all children, and in 50% of children through an additional dietary recall 7 days later. The DEI estimate will be used with a logistic regression model clustering for the repeat measure using the multilevel mixed-effects logistic regression method. This method will be implemented within STATA. It is well recognised that the dietary intake data contain a lot of uncertainty, and thus, we will conduct a sensitivity analysis using the National Cancer Institute (NCI) method calculated for usual overall average intake. We will estimate the mean and percentiles of usual energy intake distributions using the NCI method.^53 54^ This method adjusts for measurement error—primarily due to day-to-day variability in intakes—in observed, single-day estimates of nutrient intakes. We will use the NCI macros, DISTRIB and MIXTRAN, plus bootstrapped SEs for hypothesis testing.^25 27^ The MIXTRAN macro fits a mixed effects model of usual energy intake, and the DISTRIB macro uses a Monte Carlo procedure to estimate percentiles of the usual intake distribution. We will use the MIXTRAN macro to fit a model of energy intake with a fixed effect for intervention group and the DISTRIB macro to estimate usual energy intake distributions by treatment group. We will bootstrap the parameters to estimate the SE of the mean usual intakes. We will use the point estimates and SE estimates to construct 95% CIs and calculate p values for difference in mean by intervention group based on Welch’s t-test. Bootstrapped SEs will be calculated using bootstrap samples. When intake or the number of repeat recalls is low, it is common for the NCI method to fail to converge. In cases where convergence prohibits bootstrapping, we will test hypotheses using the Wilcoxon testing for clustered method.

We will also interpret the mean intake of each nutrient for the primary and secondary analysis in each arm and will present mean differences with the 95% CI for interpretation.

All analyses will be prespecified in a statistical analysis plan and posted online at Open Science Framework before analyses begin (https://osf.io/njy2a/). A per-protocol analysis will be conducted using adherence data to predefine the per protocol population. Adherence will be assessed by self-report in a 7-day recall. We will undertake two subgroup analyses: (1) by infant sex and (2) by maternal HIV status, if we find some evidence of interactions with the intervention (p<0.10).

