## Study objectives

### Objective 1

Evaluate the effect of an enhanced infant feeding intervention (‘IYCF-plus’) on energy intake at 9 months of age (window 9–11 months) in a randomised, community-based trial in rural Zimbabwe. We hypothesise that provision of powdered fortificants (PVA maize, NUA45 sugar beans, moringa and egg) for infants from 6 months of age will provide more energy at 9 months of age than the current standard-of-care IYCF intervention (trial primary outcome).

### Objective 2

Evaluate the impact of IYCF-plus on nutrient intake, growth and haemoglobin at 9 months of age (window 9–11 months) in a randomised, community-based trial in rural Zimbabwe. We hypothesise that IYCF-plus will improve the intake of key nutrients (protein, iron, zinc and folate) in 9-month-old infants compared with the standard-of-care IYCF intervention, and that IYCF-plus will increase length-for-age, weight-for-age, weight-for-length and haemoglobin more than IYCF (all secondary outcomes).

### Objective 3

Evaluate the impact of IYCF-plus on biological barriers to nutrient uptake and utilisation at 9 months of age (window 9–11 months) in a randomised, community-based trial in rural Zimbabwe. We hypothesise that the IYCF-plus intervention will increase microbiota maturity, ameliorate EED, reduce systemic inflammation and improve innate immune function in children aged 9 months, compared with the standard-of-care IYCF intervention.

### Objective 4

Identify metabolic signatures of the IYCF-plus intervention in young children at 9 months of age (window 9–11 months) in a randomised, community-based trial in rural Zimbabwe. We hypothesise that the IYCF-plus intervention will increase the concentrations of essential amino acids and choline at 9 months of age more than the standard-of-care IYCF intervention.

### Objective 5

Explore the acceptability and feasibility of the IYCF-plus intervention among participants and community stakeholders using qualitative methodology. Information from this assessment will be shared with policy makers to help design a larger roll-out of this intervention at district, provincial or national level.

### Objective 6

Explore the extent to which women’s empowerment influences IYCF practices and nutrition outcomes in rural smallholder agricultural households.

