## Follow-up data collection

Households were visited by a research nurse at 9 months of infant age (window 9–11 months) for endline data collection. If the child was not present, the visit was rescheduled. Infant weight, length, MUAC and head circumference were measured, and samples of blood, urine and stool collected, using the same methods as at baseline. Children with illness were referred to local clinics, using the same criteria as at baseline.

The trial primary outcome was measured by research nurses via 24-hour multipass dietary recall. A subgroup of 50% of randomly selected household had a second 24-hour dietary recall visit approximately 1 week later. This method provides a robust and validated measure of nutrient intake based on a comprehensive and standardised assessment.^40^ The dietary recall method assesses all food and beverages consumed in the previous 24 hours (including supplements provided by the trial) and comprises five passes. In the first pass, the research nurse asks the caregiver to list all foods consumed by the child during the previous day, and to list any night feeds. In the second pass, the caregiver is asked to list all activities they undertook, and whether they fed the child food between activities; this helps the caregiver remember all feeding episodes. In the third pass, more details about foods and beverages are collected, including the time and place of preparation, ingredients and brand of foods given. In the fourth pass, the caregiver estimates the portion size fed to the child. Research nurses carry samples of the most consumed foods and ask the caregiver to estimate the amount fed to the child. The fieldworker then transfers the estimated portion to a standard cup, spoon or digital scale for recording. In the final pass, the caregiver recalls if there were any foods or meals that have not already been mentioned. Caregivers are also asked about the general health of the child on the previous day, whether the child’s intake was less or more than usual, and how many times the child was breastfed.

Data from the 24-hour recall will be converted to observed energy and nutrient intakes by the following steps:

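### The stated analysis of continuous outcomes makes no mention of the baseline value, although growth, haemoglobin and biomarkers are measured at both visits; adjusting for it would buy precision at no cost

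*Protocol article*

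**What the plan says.** The Statistical analysis section fixes the method for continuous outcomes in one sentence: "Continuous outcomes will be compared using simple t-tests and linear regression". It adds "Robust SE estimates will be used to estimate CIs" and "P values will be two sided and interpreted as significant if p<0.05". No covariate is named for the regression, and no section of the article mentions adjustment for a baseline value.

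The outcomes this applies to include length-for-age, weight-for-age and weight-for-length Z-scores, haemoglobin and the laboratory markers (Trial outcomes, Table 2). Objective 2 states the growth and haemoglobin hypothesis as "IYCF-plus will increase length-for-age, weight-for-age, weight-for-length and haemoglobin more than IYCF (all secondary outcomes".

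The trial schedule (Baseline data collection, Table 3) marks infant anthropometry, haemoglobin, blood, stool and urine at both the baseline and the endline visit. Follow-up data collection confirms that anthropometry was repeated at endline and "samples of blood, urine and stool collected, using the same methods as at baseline". Table 6 in Laboratory analyses lists the assays at both time points. The text above that table limits them to children with samples available and calls them exploratory and unpowered. The 24-hour dietary recall is marked at endline only.

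**The concern.** A simple t-test on the endline value makes no use of where the child started. A linear regression with arm as its only term estimates the same mean difference, so it adds nothing on this point. If the child's own earlier measurement predicts the later one, leaving it out means wider intervals than the collected data allow. It also leaves chance baseline differences between two arms of about 86 in the estimate.

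The trial was sized for a binary energy outcome only, so the growth and haemoglobin comparisons have whatever precision that sample happens to give. These are the comparisons on which Objective 2 depends, and the data that would sharpen them are already scheduled.

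**Working it through.** **Inputs from the document**
- Evaluable infants: "meaning there will be an estimated 86 evaluable infants per group at endline" (Sample size).
- Allocation: "with a 1:1 allocation to IYCF or IYCF-plus" (Randomisation).
- Two-sided 5% significance (Statistical analysis).

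**Inputs the document does not give**
- The correlation r between baseline and endline values. Assumed range: 0.3 to 0.8.
- SDs for the growth, haemoglobin and biomarker outcomes. The working is therefore in SD units (SD = 1).

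**The plan's own figure first.** The Sample size section says "This sample size provides 86% power at 5% significance to detect a 20% increase in the proportion of infants achieving their recommended energy intake", against 65% in the control arm. Reading the 20% as percentage points (65% to 85%), the pooled proportion is 0.75.
- SE under the null: √(2 × 0.75 × 0.25 / 86) = 0.0660
- SE under the alternative: √((0.65 × 0.35 + 0.85 × 0.15) / 86) = 0.0642
- z = (0.20 − 1.96 × 0.0660) / 0.0642 ≈ 1.10, so power = 86.4%

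This agrees with the stated 86%. The total also agrees: 172 / 0.90 = 191.1, or 192 with equal arms. Both figures concern the binary energy outcome, which this point does not touch. They confirm 86 per arm as the right number to carry forward.

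**Precision of a continuous outcome.**
- Unadjusted SE of the difference: √(2/86) = 0.1525 SD
- Detectable difference at 80% power: (1.960 + 0.842) × 0.1525 = 0.427 SD
- With the outcome's own baseline in the model, residual variance is multiplied by (1 − r²), so the SE and the detectable difference are multiplied by √(1 − r²). The equivalent unadjusted sample is 86 / (1 − r²) per arm.

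| Assumed r | √(1 − r²) | Interval narrower by | Detectable difference (SD) | Equivalent n per arm | Power for 0.30 SD |
|---|---|---|---|---|---|
| unadjusted | 1.000 | – | 0.427 | 86 | 50.3% |
| 0.3 | 0.954 | 5% | 0.408 | 94.5 | 54.1% |
| 0.5 | 0.866 | 13% | 0.370 | 114.7 | 62.2% |
| 0.7 | 0.714 | 29% | 0.305 | 168.6 | 78.7% |
| 0.8 | 0.600 | 40% | 0.256 | 238.9 | 90.6% |

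The 0.30 SD effect in the last column is chosen only to show the shift in power; the document names no target for these outcomes.

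On the Z-score scale, assuming an SD of 1.1 for length-for-age, 0.427 SD is 0.47. It becomes 0.34 at r = 0.7 (1.1 × 0.305) and 0.28 at r = 0.8 (1.1 × 0.256).

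**The case against.** The strongest reply is that this belongs in the statistical analysis plan. The article says all analyses will be prespecified there, and that plan is not at hand. Linear regression does not exclude covariates, so the plan may already adjust for baseline. This stands in part. A reader might infer from the article that the baseline data are discarded, but the text does not say so. It says nothing about covariates. What remains is that the article does name a method, calls the t-test simple, and does not say which of the two analyses is the main one or what the regression contains.

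Second, nothing is invalid. Table 2 defines these outcomes as values at 9 months, so an endline comparison matches the endpoint. Under randomisation it is unbiased, and its interval already allows for chance imbalance. This stands in full. A reader might take Objective 2's wording about increasing more than the other arm to require a change score, but it is hypothesis wording and does not define one.

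Third, the size rests on assumed correlations. This also stands. Quoting only high values would flatter the case, and a gain plausible for length should not be carried over to variable biomarkers.

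**Conclusion.** The point holds as one of efficiency in secondary and tertiary outcomes. As the article states the analysis, the comparison is valid but less precise than the scheduled data permit. The gain from adjustment ranges from slight (5% narrower intervals at r = 0.3) to large (40% at r = 0.8). Where an outcome falls in that range depends on a correlation the document does not report.

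Three stronger readings are not supported:
- **That the primary result or sample size is affected.** Energy and nutrient intake have no baseline recall, so there is nothing to adjust for.
- **That every child has a baseline biomarker.** Those assays depend on samples being available.
- **That adjustment would bring the earlier SHINE effect of 0.16 in length-for-age within reach.** With an assumed SD of 1.1, the detectable difference at r = 0.8 is still 0.28. The SHINE effect was also measured at 18 months and is not a target set for this trial.

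**What to change.** For length-for-age, weight-for-age and weight-for-length Z-scores, haemoglobin and the biomarkers measured at both visits, name one main analysis: a linear regression of the endline value on arm and the same outcome's baseline value, with the robust standard errors already planned. Where an outcome is transformed for non-normality, transform its baseline in the same way. State a simple rule that keeps infants with an endline value but no baseline, either a missing-baseline indicator or mean imputation of the baseline. Report the unadjusted t-test as supportive. Further age and sex terms are not needed for Z-scores that are already standardised to a reference.

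The cost is a sentence or two in the analysis plan before analyses begin, and no new data. If the plan already contains this model, the article's sentence only needs to be aligned with it.

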Infant haemoglobin			x	x
Infant stool collection‡			x	x
Infant urine collection§			x	x
Endline interview form 9				x
24-hour dietary recall¶ form 10				x
Informed consent for qualitative substudies** form 11				
Qualitative substudy 1 guide form 12a				x
Informed consent for qualitative sub studies Form 11††				
Qualitative substudy 2 guide form 12b				x

*Trial enrolment began in April 2021 and concluded in August 2021.

†For mothers who wish to provide informed consent on a subsequent day to screening, these visits will be separated.

‡Target date 9 months of infant age (visit window 9–11 months or 274–334 days).

§If any specimens cannot be collected during the visit (eg, if the infant fails to pass stool), the specimen collection will be rescheduled for the next day, or as soon as possible after the visit. Rarely it may be necessary to repeat a specimen collection if the sample was insufficient, or fails quality control checks during processing in the laboratory. All blood draws will be kept to a safe limit, defined as maximum of 1 mL/kg body weight.

¶The primary outcome, measured by multipass 24-hour dietary recall, will be repeated 1 week later in a subsample of 50% infants for methods validation.

**Subgroup of up to 20 purposively selected households. The social scientist will visit the family during a separate visit at 7–9 months (214–273 days) of infant age, and obtain separate written informed consent for the qualitative interviews.

††Subgroup of up to 30 purposively selected households. The social scientist will obtain written informed consent for the qualitative interviews regarding migration, which will be conducted throughout the course of the study.

IYCF, infant and young child feeding; MUAC, mid-upper arm circumference.

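### The primary model yields a child-specific odds ratio, while the trial is sized on a difference in percentages and no step back to percentages is stated

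*Protocol article*

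**What the plan says.** - **Design target.** The Sample size section plans 86 evaluable infants per arm "to detect a 20% increase in the proportion of infants achieving their recommended energy intake", "assuming that only 65% of infants are meeting requirements in the IYCF (standard-of-care) arm based on SHINE data".
- **Primary model.** The Statistical analysis section takes the percentage of infants meeting the energy requirement as the primary outcome. All children have one 24-hour recall and 50% have a second about a week later. The model is logistic, "clustering for the repeat measure using the multilevel mixed-effects logistic regression method".
- **Effect measure.** For binary outcomes in general, the same section names a chi-squared test and "logistic regression to compute ORs and corresponding 95% CIs", with robust standard errors. It does not name the unit of clustering.
- **Other summaries.** The mean differences with 95% CI promised in that section concern mean intake. The NCI-method sensitivity analysis tests a difference in mean usual intake. Neither returns the primary model to the percentage scale.
- **Repeat recall.** A Table 3 footnote says the recall "will be repeated 1 week later in a subsample of 50% infants for methods validation".
- **Shared households.** Under Randomisation: "Twins or eligible infants within the same household were allocated to the same trial arm".

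The Trial outcomes section words the primary outcome as energy intake in kcal. This point concerns the percentage version, which the Sample size and Statistical analysis sections use.

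**The concern.** The design asks how many more infants in 100 meet their requirement. A random-intercept logistic model answers a different question: by what factor the odds change for a child with a given intercept. The two answers are linked only through the between-child variance on the logit scale. So the same pair of percentages gives different odds ratios in populations that differ only in how similar a child's intake is from day to day. That variance can be learned only from children with two recalls, here half the sample.

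At stake is how the result is read. The Dissemination section sends the findings to the health ministry and to UNICEF. A headline odds ratio that depends on day-to-day correlation cannot be compared with the 20-point target without a further calculation, and the article does not name one.

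**Working it through.** **1. Reproduce the stated power.** Inputs from Sample size and Statistical analysis: 86 per arm, 0.65 vs 0.85, two-sided 5%. With pooled variance under the null and mean proportion 0.75:

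- null SE = sqrt(2 × 0.75 × 0.25 / 86) = 0.0660
- alternative SE = sqrt((0.65 × 0.35 + 0.85 × 0.15) / 86) = 0.0642
- power = Φ((0.20 − 1.96 × 0.0660) / 0.0642) = Φ(1.10) = 86.4%, against 86% stated

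Reading the 20% as relative (65% to 78%) gives 47%. The design target is therefore an absolute difference of 20 points. Numbers also agree: 192 × 0.9 / 2 = 86.4 per arm.

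**2. Marginal measures for 65% vs 85%.** Risk difference 20 points; risk ratio 0.85/0.65 = 1.31; odds ratio (0.85/0.15)/(0.65/0.35) = 3.05. None depends on the within-child correlation.

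**3. Conditional odds ratio for the same percentages.** The correlation is an assumption, shown as a range. For latent ICC ρ, the random-intercept variance is σ² = ρ/(1−ρ) × π²/3. In each arm, solve for the intercept at which the logistic probability, averaged over a normal random effect with variance σ², equals 0.65 or 0.85. Then exponentiate the difference between the two intercepts.

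| Assumed ICC | σ² | Conditional OR | Ratio to 3.05 |
|---|---|---|---|
| 0 | 0 | 3.05 | 1.00 |
| 0.1 | 0.37 | 3.28 | 1.07 |
| 0.3 | 1.41 | 3.94 | 1.29 |
| 0.5 | 3.29 | 5.18 | 1.70 |

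A hand check uses the usual approximation log OR(conditional) ≈ log OR(marginal) × sqrt(1 + 0.346σ²). With log 3.05 = 1.116 it gives 3.27, 3.90 and 5.11, close to the exact values.

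**4. The reverse reading.** From a 65% base, a conditional odds ratio of 3.05 corresponds to a gain of 20.0 points at ICC 0, 17.1 at 0.3 and 14.6 at 0.5. The coefficient alone does not fix the change in percentage.

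**5. Precision.** Trials were simulated with 86 per arm, half with two recalls, and true percentages of 65% and 85%. The 5th to 95th percentiles of the fitted values were about:

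| Assumed ICC | Mixed-model OR | Upper/lower |
|---|---|---|
| 0.1 | 2.0 to 6.0 | 3.0 |
| 0.3 | 2.1 to 7.8 | 3.7 |
| 0.5 | 2.2 to 15.9 | 7.2 |

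The marginal odds ratio ran from about 1.8 to 5.4 (upper/lower 3.0) and the risk difference from about 0.10 to 0.29. The extra imprecision is negligible at ICC 0.1, moderate at 0.3 and large at 0.5. The source is the intercept SD. At ICC 0.5 its true value is sqrt(3.29) = 1.81, while its estimate ranged from 0.96 to 3.15.

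**6. Validity of the test.** With no effect (300 simulated trials per setting), the mixed-model likelihood-ratio test rejected in 4.7% of trials at ICC 0.2 and 5.0% at ICC 0.5. With 65% vs 85% its power was 95% and 93%, against 85% and 87% for chi-squared on the first recall alone. In a separate set of 250 trials per setting, a risk difference with clustered standard errors had power 95% vs 96% for the mixed model at within-child correlation 0.3, and 91% vs 91% at 0.5.

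**The case against.** - **An odds ratio beside a chi-squared test is conventional, and the test works.** Both are true. The mixed model uses every recall, holds its error rate, and gains power over the first recall alone. A reader might infer that the primary test is invalid or the trial underpowered; the calculations show neither.
- **The odds ratio does not overstate the difference in percentages, because the scales differ.** This stands. The fair comparator is the marginal odds ratio of 3.05. That figure is already well above the risk ratio of 1.31 because the outcome is common, and a plain logistic odds ratio shares that feature.
- **The size rests on a correlation the article does not give.** This stands too. The excess over the marginal odds ratio is 7% at ICC 0.1, 29% at 0.3 and 70% at 0.5. A reader might infer a severalfold exaggeration; the article gives no basis for one.
- **The conversion is a detail for the analysis plan.** Partly. The article says a plan will be posted before analysis, the percentages will be calculated, and it never says the mixed-model odds ratio will be the only or headline result. But the article itself chose the model and names odds ratios for binary outcomes, so it has already fixed a scale that differs from its design target.
- **Table 3 and the household are side issues.** Agreed. The footnote does not say the repeat recall is only for validation. It is tempting to say the plan ignores the household, but it promises robust standard errors without naming the cluster, and silence is not a decision. The number of shared households is not given, and no effect on the result has been shown.

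**Conclusion.** The point holds as one about the effect measure. The design target is a marginal difference of 20 percentage points; the named primary model delivers a conditional odds ratio, and the article gives no route from one to the other. The mismatch is small if a child's two recall days are weakly correlated and substantial from an ICC of about 0.5, where the fitted odds ratio is also unstable. These sizes assume true percentages of 65% and 85%, a normal random intercept, 86 evaluable infants per arm, a second recall in half of them, and the stated ICC range. The conclusion on statistical significance would not be expected to change. This is an inexpensive improvement, not a correction of an invalid analysis.

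**What to change.** For the percentage meeting the energy requirement, name as the main effect measure the population-averaged percentage in each arm and their risk difference with 95% CI. Obtain them from logistic regression or GEE on all recalls, standardised by arm, with robust standard errors clustered on household. That one choice covers repeat recalls and infants of the same household. The Follow-up data collection section says the households for the second recall were randomly selected, so pooling all recalls should not bias the percentages. Keep the mixed-model odds ratio as a supplementary result if wanted.

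Minor: align the Table 3 footnote with the Statistical analysis section by saying that the repeat recall also enters the primary analysis.

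Cost: a sentence in the plan, a little more analysis work, and a change of headline effect measure. No new data are needed, and the simulations show no meaningful loss of power.
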